### Sample Size

Sample size calculations were based on the minimum detectable effect (MDE) to assess changes in sanitation coverage, the primary outcome measure, at the project end line. Data for all parameters used in sample size calculations were drawn from the baseline survey conducted by World Vision before the implementation of the W4E project between January and April 2021. For the MDE calculation, we assumed a 2-tailed test with a significance level of 0.05 and a power of 0.8. We assumed a conservative intracluster coefficient of 0.1 [30]. As baseline data indicates that the average percentage of households with at least unimproved sanitation coverage across Chiradzulu District was 67%, power calculations assumed a total enrollment of 20 intervention clusters in each TA receiving interventions and 30 clusters selected from the control arm of the study. Assuming an average of 20 households surveyed per selected cluster results in an MDE of 0.136 or an average difference of 13.6 percentage points in sanitation coverage (relative change in coverage of 19%) between either arm of intervention clusters and the control cluster. Therefore, the study aims to recruit a total of 1400 households (CLTS+CG: n=400; CLTS only: n=400; Control: n=600; Figure 2) at each data collection round.

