### Study Outcomes

The primary outcome is sanitation coverage. Secondary outcomes include basic sanitation coverage, sanitation use, sanitation-related quality of life, latrine quality, presence of a handwashing facility, handwashing behavior, and safe disposal of child feces (Multimedia Appendix 3).

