### Analysis

Statistical analysis will be carried out at the individual or household levels with appropriate adjustments for clustering within villages (and within households for individual-level outcomes). Data will be analyzed according to the TA and intervention assignment irrespective of whether the intervention was taken up fully, partly, or not at all. Since this is an effective study, only an intention-to-treat dataset will be maintained.

The primary estimates of the effectiveness of the intervention on primary and secondary outcomes will be based on a difference-in-difference analysis and models adjusted for design variables alone (TA, village population above or below TA-specific median); a fixed effect for village size (above or below the median) will be included in the model. All models will include a dummy variable for the treatment arm (ie, CLTS, CLTS+CG, or control) and data collection round (baseline and end line) as well as the interaction term of those 2 variables.

To account for the clustering of observations, hierarchical mixed-effects models will be used for all analyses. For household-level outcomes or outcomes where there is only one respondent per household, mixed effects models will account for clustering by including a random effect at the village level. For outcomes with multiple respondents or data points per household (specifically sanitation use, and hand washing behavior), an additional random effect will be added at the household level.

All analysis of primary and secondary outcomes will be based on the difference-in-difference approach. The regression coefficient of the interaction term between the treatment arm and the data collection round will be used as the primary effect measure. For binary outcomes measure, we will use melogit with robust SEs and regression coefficients exponentiated to estimate an odds ratio (OR). For continuous outcomes, we will use meglm, with identity link and Gaussian family.

The results will be presented with 95% CIs. Analyses will report on ORs and 95% CIs of each treatment arm compared to the control as well as the CLTS alone compared to CLTS+CG. Secondary outcomes include the following:

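### Near-ceiling, unequal baselines make the odds ratio alone a scale-dependent and possibly non-estimable effect measure for sanitation coverage; a percentage-point difference-in-differences should be prespecified beside it

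*Protocol article*

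**What the plan says.** Study Outcomes states: "The primary outcome is sanitation coverage". The full definition is in Multimedia Appendix 3, which is not shown. The Sample Size section indicates what is meant, because it plans from the figure that "the average percentage of households with at least unimproved sanitation coverage across Chiradzulu District was 67" percent.

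The same section works on the absolute scale. The detectable effect is "an average difference of 13.6 percentage points in sanitation coverage" between either intervention arm and control. On the assumptions, "we assumed a 2-tailed test with a significance level of 0.05 and a power of 0.8" and "We assumed a conservative intracluster coefficient of 0.1".

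The Analysis section works on another scale:
- "The regression coefficient of the interaction term between the treatment arm and the data collection round will be used as the primary effect measure".
- The model for binary outcomes is given thus: "we will use melogit with robust SEs and regression coefficients exponentiated to estimate an odds ratio (OR").
- "Analyses will report on ORs and 95% CIs of each treatment arm compared to the control as well as the CLTS alone compared to CLTS+CG".

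For binary outcomes it names no risk difference and no contrast of marginal probabilities. An identity-link model (meglm) is planned, but only for continuous outcomes.

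**The concern.** A difference-in-differences assumes that, without the intervention, the arms would have moved in parallel. When baselines differ, parallel movement in log-odds and parallel movement in percentage points are different assumptions. Close to 100% they diverge sharply. The baselines here are both unequal and close to 100%. Traditional authorities were assigned without randomisation, one per arm, so the design does not remove the inequality.

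Two things are at stake. First, the direction and size of the reported effect can turn on a choice of scale that the article does not discuss, while its sample size is expressed on the other scale. This includes the main comparison of CLTS+CG with CLTS alone, since CLTS starts higher. Second, CLTS aims to end open defecation. An arm in which every sampled household has a facility at end line would leave its logistic interaction without a finite estimate.

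**Working it through.** **Planned figure.** Inputs from Sample Size: 67% coverage, 20 and 30 clusters of 20 households, ICC 0.1, two-sided 0.05, power 0.80. The design effect is 1 + 19 × 0.1 = 2.9, so the effective sizes are 600/2.9 = 206.9 and 400/2.9 = 137.9. A two-proportion test with pooled variance reaches 80% power at an increase of 0.1358. The stated 0.136 is reproduced (power 80.1%), and it is a calculation on the absolute scale.

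**Baselines (Table 2; basic + limited + unimproved).**
- Control: (26 + 55 + 483)/600 = 564/600 = 94.00%; 36 without a facility.
- CLTS+CG: (43 + 64 + 278)/400 = 385/400 = 96.25%; 15 without.
- CLTS: (28 + 30 + 333)/400 = 391/400 = 97.75%; 9 without.

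**Equal gain in points.** The difference-in-differences in points is zero. The odds ratio is [odds(p_T + g)/odds(p_T)] / [odds(p_C + g)/odds(p_C)]. For g = 1 point the within-arm odds ratios are 1.213 (control), 1.378 (CLTS+CG) and 1.818 (CLTS), so CLTS against control is 1.818/1.213 = 1.50.

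| Equal gain | CLTS vs control | CLTS+CG vs control | CLTS+CG vs CLTS |
|---|---|---|---|
| 1 point | 1.50 | 1.14 | 0.76 |
| 1.5 points | 2.25 | 1.25 | 0.56 |
| 2 points | 6.00 | 1.43 | 0.24 |

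With a village random intercept at a latent ICC of 0.1 (variance (0.1/0.9) × π²/3 = 0.366), the control contrasts at 1 and 2 points are unchanged to two decimals.

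**Equal halving of the no-facility share.** The gains are 3.000 (control), 1.875 (CLTS+CG) and 1.125 (CLTS) points. The within-arm odds ratios are 2.064, 2.039 and 2.023.
- CLTS vs control: odds ratio 2.023/2.064 = 0.98; points 1.125 - 3.000 = -1.9.
- CLTS+CG vs control: odds ratio 2.039/2.064 = 0.99; points 1.875 - 3.000 = -1.1.

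Each scale therefore shows a null where the other does not.

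**Ranking of the two interventions.** If CLTS+CG gains 2.0 points and CLTS 1.5, CLTS+CG is ahead by 0.5 point. The odds ratio is [odds(0.9825)/odds(0.9625)] / [odds(0.9925)/odds(0.9775)] = 2.187/3.046 = 0.72, in favour of CLTS.

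**Precision.** In the 2-point case CLTS goes from 9 to 1 household without a facility, and control from 36 to 24. The variance of the log odds ratio, ignoring clustering, is 1/36 + 1/564 + 1/24 + 1/576 + 1/9 + 1/391 + 1/1 + 1/399 = 1.189, so the SE is 1.09 and the 95% CI is 0.71 to 50.8. The single remaining household supplies most of the variance.

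**Empty cell.** At 400/400 the likelihood keeps rising as the interaction grows. A plain logistic fit showed coefficients of 7.4, 17.4 and 33.4 with more iterations, and an SE rising from 9.9 to over 3 million. A village random intercept adds no failures to that cell. The chance of 400/400 depends on true end-line coverage, which the article does not give, so these are assumed values. The lower figure treats households as independent (p^400). The upper is beta-binomial, 20 villages of 20, ICC 0.1.

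| True coverage (assumed) | Chance of 400/400 |
|---|---|
| 98.5% | 0.2% to 4% |
| 99% | 2% to 11% |
| 99.5% | 13% to 34% |
| 99.8% | 45% to 65% |

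**Sanitation use (Table 2).** 2201/2338 = 94.1%, 1480/1520 = 97.4% and 1502/1528 = 98.3%. An equal 1-point gain gives an odds ratio of 2.450/1.219 = 2.01 for CLTS against control. There are 137, 40 and 26 non-users, so an empty cell is a different and separate risk, not computed here.

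**The case against.** The strongest reply is that this is scale dependence, not an error. Parallel trends in log-odds are a legitimate assumption, and sizing in points while analysing with a logit model is not a contradiction. In the 2-point example CLTS loses 8 of 9 households without a facility (89%) and control 12 of 36 (33%), so an odds ratio above 1 describes something real. This stands. A reader might infer that the odds ratio is wrong and that points should replace it as the primary measure. The documents do not support that. Nothing in them makes equal point gains the true null, and near the ceiling the point scale has the mirror defect: if every arm reached 100%, CLTS would show 2.25 - 6.00 = -3.75 points against control and CLTS+CG 3.75 - 6.00 = -2.25.

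A reader might also infer that full success leaves the trial with no estimate, or that the odds ratio would produce a false claim of success. Both go too far. If one intervention arm reaches 400/400, only contrasts with that arm are lost. In the 2-point case the chance of p < 0.05 for CLTS against control is about 38% ignoring clustering and 16% with the design effect of 2.9. The likelier harm is an unstable or misleading point estimate. The article also notes that Malawian communities find full coverage hard to sustain, so the higher rows of the empty-cell table may not arise.

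Finally, an unseen analysis plan could hold an empty-cell rule or supporting risk differences. That is fair, and their absence alone is not the finding. The finding is that the article fixes the odds ratio as the sole measure for binary outcomes where its own baselines make a single scale uninformative.

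**Conclusion.** The point holds as a limited one. With baselines of 94.0%, 96.25% and 97.75%, the odds ratio alone cannot carry the primary conclusion. It moves from 1.00 to between 1.50 and 6.00 (CLTS against control) under equal gains of 1 to 2 points, is very imprecise with so few households left, and does not exist for contrasts with an arm that reaches 400/400. A point difference alone would not be adequate either. Both scales are needed.

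The main assumption is that sanitation coverage means at least unimproved. Sample Size supports this, but the outcome appendix is not shown, and the abstract illustrates sanitation coverage with the unimproved category only. If only that category counted (80.5%, 69.5% and 83.25% in control, CLTS+CG and CLTS), an equal 10-point gain would still give odds ratios of 0.74 (CLTS+CG) and 1.20 (CLTS) against control, but the ceiling and empty-cell problems would be much weaker.

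Reporting both scales does not cure a separate limit: the room left is at most 6.0, 3.75 and 2.25 points, so a 13.6-point gain cannot occur on this definition.

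**What to change.** In the Analysis section, for sanitation coverage and sanitation use:

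1. Prespecify a percentage-point difference-in-differences with village-clustered SEs, reported beside the melogit odds ratio for all three contrasts. It can come from an identity-link model or from marginal predictions of the logit model.
2. State that the identity-link difference-in-differences is the estimate used if an arm-by-round cell has no failures.
3. State that any claim of effect will be read in light of both scales and each arm's remaining room to improve.
4. Confirm the definition of sanitation coverage in the main text, since the force of this point depends on it.

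The cost is a few sentences and a few lines of code, with no new data; meglm with an identity link is already in the plan. There are real downsides. The two measures may disagree and the report must then explain why, the point scale works against arms with higher baselines, and a linear model can give fitted values above 1 at about 98% coverage.

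### Continuous secondary outcomes: with only a village intercept and no robust SEs named, the difference-in-difference intervals will tend to be too narrow if villages change differently between rounds

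*Protocol article*

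**What the plan says.** The Analysis section of the protocol article makes the arm-by-round interaction the effect measure for all primary and secondary outcomes. For household-level outcomes, and those with one respondent per household, "mixed effects models will account for clustering by including a random effect at the village level". No village-by-round effect or random slope for round is mentioned.

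The section then names the commands. Binary outcomes get melogit with robust SEs. The next sentence reads: "For continuous outcomes, we will use meglm, with identity link and Gaussian family". It names no SE type.

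The outcome list in the same section defines two continuous outcomes, both secondary: the SanQoL-5 index, with one respondent per household, and the latrine quality score from a principal components analysis. The primary outcome, sanitation coverage, is binary.

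**The concern.** A single village intercept assumes that a village departs from its arm's mean by the same amount at baseline and at end line. In a before-after contrast that common departure subtracts out. The model-based SE of the interaction then reflects almost only household sampling variation, as if all villages in an arm shifted in step.

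That is a strong assumption here. The section Selection of Clusters and Households describes villages as the units in which CLTS is delivered, and Description of the Intervention has facilitators and local leaders running the triggering sessions. Uneven uptake from village to village is to be expected. If it occurs, the planned SE for SanQoL-5 and latrine quality leaves out a real source of variation, and chance differences reach nominal significance more often than 5% of the time. SanQoL-5 is among the secondary outcomes named in the abstract, and no multiplicity adjustment is planned, so these intervals will be read at face value.

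**Working it through.** **Inputs from the Sample Size section.** The test is two-sided at 5% with 80% power. On clustering, the article says: "We assumed a conservative intracluster coefficient of 0.1". That ICC is given for sanitation coverage; none is given for the continuous outcomes. There are 20 villages in each intervention arm and 30 in the control arm, with 20 households per village in each round. From Table 2, the overall baseline SD of SanQoL-5 is 0.25.

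**Assumptions not in the documents.** CAC (cluster autocorrelation, the correlation of a village's effect between rounds) from 0.5 to 1; an alternative ICC of 0.05; fresh households in each round.

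**The plan's own figure.** The design effect is 1 + (20 − 1) × 0.1 = 2.9. Effective sample sizes are 400/2.9 = 137.9 and 600/2.9 = 206.9. Solving the two-proportion formula with pooled variance under the null (z values 1.96 and 0.84) upward from 67% gives a difference of 0.1358, which matches the stated 0.136. This confirms how the ICC and cluster size were used. The figure concerns coverage at end line and does not test the continuous models.

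**Variance of the interaction.** Let m = 20 households per village per round, and let k1 and k0 be the numbers of villages in the two arms compared.

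- True variance: 2 × SD² × [ICC(1 − CAC) + (1 − ICC)/m] × (1/k1 + 1/k0).
- Variance reported by the village-intercept model, to a close approximation: 2 × SD² × [(1 − ICC × CAC)/m] × (1/k1 + 1/k0).

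The factor (1/k1 + 1/k0) is common to both, so the ratio of SEs is the same for either arm against control and for CLTS against CLTS+CG. The type I error of a nominal 5% test is 2 × [1 − Φ(1.96 × ratio)].

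| ICC | CAC | True bracket | Model bracket | Model SE / true SE | Type I error |
|---|---|---|---|---|---|
| 0.1 | 1.0 | 0.0450 | 0.0450 | 1.00 | 5% |
| 0.1 | 0.9 | 0.010 + 0.045 = 0.0550 | 0.91/20 = 0.0455 | 0.91 | 7.5% |
| 0.1 | 0.8 | 0.020 + 0.045 = 0.0650 | 0.92/20 = 0.0460 | 0.84 | 10% |
| 0.1 | 0.5 | 0.050 + 0.045 = 0.0950 | 0.95/20 = 0.0475 | 0.71 | 17% |
| 0.05 | 0.8 | 0.010 + 0.0475 = 0.0575 | 0.96/20 = 0.0480 | 0.91 | 7% |
| 0.05 | 0.5 | 0.025 + 0.0475 = 0.0725 | 0.975/20 = 0.04875 | 0.82 | 11% |

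**Simulation check.** 20,000 simulated trials per setting, with 30, 20 and 20 villages and the residual variance the model would estimate, gave type I errors of 7.5%, 10.2% and 17.0% for arm against control at ICC 0.1 and CAC 0.9, 0.8 and 0.5. The SE shortfall at CAC 0.5 was 30%, against 29% from the approximation. SEs built from village-level changes, which behave like village-clustered robust SEs, held type I error between 5.4% and 5.9% in every setting.

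**On the SanQoL-5 scale.** For an arm against control (20 and 30 villages) at ICC 0.1, the model SE stays near 0.022 at every CAC. The correct SE is 0.0217 at CAC 1, 0.0239 at 0.9, 0.0260 at 0.8 and 0.0315 at 0.5.

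**The case against.** **The SE type is not stated.** The article does not say that model-based SEs will be used. That is inferred from robust SEs being named for melogit and not for meglm in the next sentence, and from the command's default. The section also promises suitable adjustment for clustering within villages. If robust SEs are meant for both commands, the understatement does not arise. This stands as a limit. It does not dispose of the point, because the article fixes command, link, family and random effect, and that model as written has no term for village-specific change.

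**The size is assumed.** No CAC is given, and the ICC of 0.1 is described as conservative and belongs to another outcome. This stands, and the result is a range that includes zero error at CAC 1.

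**Control villages receive CLTS only after the end line,** so uneven triggering cannot act there. If only intervention villages change unevenly, type I error for an arm against control at ICC 0.1 falls to about 8% at CAC 0.8 and 12-13% at CAC 0.5. That is smaller, but not nil, and control villages may drift for other reasons.

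**The same households may have been re-surveyed.** An unmodelled household correlation makes the model SE too large and works against the error. At CAC 0.8, setting ICC(1 − CAC) + (1 − ICC)(1 − r)/20 equal to the model bracket gives cancellation at r of about 0.42 for ICC 0.1, and about 0.20 for ICC 0.05; a larger r reverses the error. The recruitment target at each round (Sample Size) and the absence of recorded identifiers (Data Management) suggest fresh samples, but the article does not say so. Village-clustered SEs cope with either case.

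**Stronger readings.** A reader might infer that the primary result is affected as well. The documents do not support that: coverage is binary and robust SEs are stated for it. Nor do they support saying that these two outcomes will be over-called, since that depends on villages changing differently.

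**Conclusion.** The point holds in conditional form and for two secondary outcomes only. As written, the model for SanQoL-5 and latrine quality gives intervals that tend to be too narrow if villages change differently between rounds. With fresh samples, 20 households per village and ICC 0.1, the SE is about 9% to 29% too small for CAC from 0.9 to 0.5, and nominal 95% intervals cover about 92.5% to 83%. At ICC 0.05 the type I error is about 7% at CAC 0.8 and 11% at CAC 0.5. The default SE, the CAC, the ICC for these outcomes and the fresh sampling are all assumptions. It is worth correcting because the plan already uses the remedy for its binary outcomes.

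**What to change.** State that the continuous outcomes will also use robust SEs, clustered on village. Alternatively, or in addition, add a village-by-round random effect to those two models. Extending that term to the binary models is optional, since no SE defect is shown there. It would also help to state whether end-line households are new or re-surveyed.

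The change needs no new data: one SE option, one random term, or both. The cost is wider CIs for these two outcomes, by roughly 10% to 40% under the assumptions above (1/0.91 = 1.10; 1/0.71 = 1.41). With few villages per arm, robust SEs may still run slightly liberal (5.4% to 5.9% in the simulation).

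None of these changes addresses differential change at the level of the traditional authority (TA). With one TA per arm, that stays unmeasured, and the report should say so.

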### Data Collection

A baseline survey was conducted in all 3 TAs between May and June 2023 before intervention implementation in TA Chitera (CLTS+CG group) and TA Ntchema (CLTS group). An end-line survey was conducted in all 3 TAs between March and April 2024. TA Nkalo (control group) received the CLTS intervention after the end-line survey. A structured questionnaire with closed-ended questions with precoded responses on mobile devices on the KOBO collect platform (KoboToolbox) was used to collect data on household membership, wealth index, sanitation and hygiene facilities, and child health (Multimedia Appendix 2). Further, the enumerators conducted spot checks and recorded hygiene proxy measures, such as the presence and state of a latrine, presence, location, and type of handwashing facility (including the availability of soap and water). The interviews were conducted in Chichewa, the local language of Chiradzulu District. Chichewa-speaking enumerators with extensive training and expertise administered the structured questionnaire.

To confirm the availability of WASH infrastructure and hygiene practices, we conducted structured observations in 350 selected households (ie, 100 households from each intervention arm and 150 households from the control group) among the recruited 1400 households. A line listing of the 1400 households was created and a Microsoft Excel random generation number was run to identify the 350 households for observations. Specifically, the observations were intended to capture practices pertaining to the presence of latrine and handwashing facility with soap, handwashing practice at critical times (ie, before eating, before food preparation, after changing the child's nappy, and after latrine use), and child feces disposal. One observer was placed at each selected household. As behaviors of interest mostly occur in the morning hours to noon [31], observations lasted 4 hours from 8 AM to noon. The observer first conducted the structured observations after which he or she proceeded to administer the structured questionnaire.

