Sanitation use: measured as an individual-level binary indicator based on the reported location last time each member of the household used a latrine.Safe disposal of child feces: will be analyzed as a mixed effect model (household, village, and cluster) of observed household disposal sites of last defecation for all children under the age of 5 years.Basic sanitation coverage: this is a household-level indicator based on the presence of an observed sanitation facility that meets Joint Monitoring Programme (JMP) criteria for basic sanitation facilities, specifically an improved sanitation type.Sanitation-related Quality of Life (SanQoL-5): SanQoL-5 index is an individual-level variable reported by only one participant per household. It is a continuous variable (0-1) based on the weighted score of responses to 5 questions on a 3-level frequency scale [32].Latrine quality: latrine quality is a composite index based on observed and reported characteristics of household latrines [8]. Specific binary indicators will be combined using principal components analysis (PCA) and iteratively refined using standard approaches to index development. Outcomes will be analyzed as a continuous variable based on the PCA score.Basic handwashing facility: the presence of handwashing where both soap and water are available is a household-level binary variable. This will be analyzed in two ways: (1) both observed and reported handwashing facility (HWF) with both soap and water available at the time of data collection and (2) observed HWF with soap and water.Handwashing behavior: A binary outcome measure based on structured observation data. Structured observation data will be used to identify all predefined hand hygiene opportunities (eg, before food preparation, before eating, before feeding a child, after using a latrine, after cleaning a child, and after being in contact with an animal) and associated hand hygiene (0=no hand hygiene or hand hygiene with water only; 1=hands washed with soap). The analysis will be conducted at the event level with adjustment for repeated observations within the same household.

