**Handwashing facility available (reported or observed), n/n (%)**					
	Basic^b^	104/1400 (7)	59/600 (10)	15/400 (4)	30/400 (8)
	Limited^c^	683/1400 (49)	309/600 (52)	168/400 (42)	206/400 (52)
	No handwashing facility	613/1400 (44)	232/600 (39)	217/400 (54)	164/400 (41)

^a^Joint Monitoring Programme.

^b^Basic handwashing facility: handwashing facility with soap and water.

^c^Limited handwashing facility: handwashing facility with no soap or water.

A total of 1099 hand hygiene structured observations were conducted across the 3 TAs (Table 3). Specifically, 330 structured observations were conducted in TA Chitera (CLTS+CG), 295 in TA Ntchema (CLTS), and 474 in TA Nkalo (control). The median number of observed hand hygiene opportunities per household was 3. Most households did not practice hand hygiene or wash hands with water at specific hand hygiene junctures (eg, after using the toilet, before food preparation, before eating, before feeding a child, and after being in contact with an animal; Table 3). A total of 73 child feces disposal structured observations were conducted across the 3 TAs, with 26 in the CLTS+CG group, 18 in the CLTS, and 29 in the control. Overall, approximately half of the households safely disposed of child feces (Table 3).

**Table 3 table3:** Hand hygiene and child feces disposal structured observations.

Characteristics			All participants (N=1099)		Control (TA Nkalo) (n=474)		CLTS+CG (TA Chitera) (n=330)		CLTS (TA Ntchema) (n=295)

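### Handwashing behavior: the closed list of hand-hygiene opportunities conflicts with the outcome definition, and the event-level model has no term for opportunity type, so an arm-specific change in event mix would move the interaction OR

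*Protocol article*

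**What the plan says.** The article describes the hand-hygiene occasions in three places.

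- **Methods, Data Collection**, on what the structured observations were meant to capture: "handwashing practice at critical times (ie, before eating, before food preparation, after changing the child's nappy, and after latrine use". The *ie* makes this a closed list of four.
- **Methods, Analysis**, definition of handwashing behavior: "Structured observation data will be used to identify all predefined hand hygiene opportunities". Six examples, introduced by *eg*, then follow: "before food preparation, before eating, before feeding a child, after using a latrine, after cleaning a child, and after being in contact with an animal".
- **Results**, text before Table 3, on the baseline observations. Five examples, again introduced by *eg*, are given: "after using the toilet, before food preparation, before eating, before feeding a child, and after being in contact with an animal".

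The outcome is binary per event (soap or not): "The analysis will be conducted at the event level with adjustment for repeated observations within the same household". On model terms, Analysis says "All models will include a dummy variable for the treatment arm (ie, CLTS, CLTS+CG, or control) and data collection round (baseline and end line"), together with their interaction. It adds a fixed effect for village size and random effects for village and, for this outcome, household. Adjustment for Covariates adds variables at respondent, household and community level. The effect measure is the exponentiated interaction coefficient. No section names opportunity type as a covariate, stratum or standardising variable, and Table 3 is not split by type.

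**The concern.** The set of opportunities is the denominator of this outcome. An analyst who follows Data Collection drops feeding and animal-contact events; one who follows the outcome definition keeps them. The two would compute different proportions from the same observation sheets.

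The second part follows from pooling. Soap use plausibly depends on the occasion, for example after latrine use versus before eating. If so, the pooled proportion depends on which kinds of event were seen as well as on what people did. Each household is watched from 8 AM to noon in a round, with a median of 3 events. Each arm is a single traditional authority (TA), so a change in event mix particular to one TA between May-June 2023 and March-April 2024 cannot be told apart from an arm effect on the pooled OR. The village and household random effects model correlation and do not remove such a shift.

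**Working it through.** **1. The lists side by side**

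| Occasion | Data Collection (closed) | Outcome definition (examples) | Baseline results (examples) |
|---|---|---|---|
| Eating | yes | yes | yes |
| Food preparation | yes | yes | yes |
| Latrine or toilet use | yes | yes | yes |
| Nappy change / cleaning a child | yes (nappy) | yes (cleaning) | not named |
| Feeding a child | **no** | **yes** | **yes** |
| Animal contact | **no** | **yes** | **yes** |

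The firm conflict is in the last two rows. A closed list leaves out two event types that both other places count.

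**2. Reproducing the baseline figures (Table 3)**

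- Events: 474 + 330 + 295 = 1099.
- Soap and water: 36/1099 = 3.28% overall; control 12/474 = 2.53%; CLTS+CG 17/330 = 5.15%; CLTS 7/295 = 2.37%. These agree with the rounded percentages in Table 3.
- Mean events per observed household: 1099/350 = 3.14 (control 474/150 = 3.16; CLTS+CG 330/100 = 3.30; CLTS 295/100 = 2.95).

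**3. What a mix shift does to the OR (illustration only)**

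The article gives neither event counts nor soap rates by type, so the inputs below are assumptions. Let a share *s* of events be of a high-soap type with rate *hi*, and the rest have rate *lo*. Then

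pooled rate = *s* × *hi* + (1 − *s*) × *lo*.

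Hold *hi* and *lo* fixed (no change in behavior), choose *s* so that the pooled rate is 36/1099, and raise *s* in one arm only at end line. The other arm does not move, so that arm's end-line versus baseline OR is the spurious interaction OR.

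Example with 10% v 1%: starting *s* = (0.0328 − 0.01)/0.09 = 0.253. With 10 points more, the pooled rate is 0.0328 + 0.10 × 0.09 = 0.0418, and the OR is (0.0418/0.9582)/(0.0328/0.9672) = 1.29.

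| Assumed *hi* v *lo* | +5 points | +10 points | +20 points |
|---|---|---|---|
| 6% v 2% | 1.06 | 1.13 | 1.25 |
| 8% v 1% | 1.11 | 1.22 | 1.45 |
| 10% v 1% | 1.14 | 1.29 | 1.58 |
| 15% v 1% | 1.22 | 1.45 | 1.91 |

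If *hi* = *lo*, every entry is 1.00. With a term for opportunity type in the model, the conditional OR is 1.00 in every scenario, because no type-specific rate has changed.

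**4. Scale against chance (CLTS v control, ignoring clustering)**

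- Share of one type, taken as 30%, with baseline event counts in both rounds: the SE of the difference-in-difference in share is √[2 × 0.21 × (1/295 + 1/474)] = 0.048. A one-arm shift of 10 points is about 2 SE, and 20 points is more than 4 SE.
- Log interaction OR, assuming end-line counts like those at baseline: √[2 × (1/7 + 1/288 + 1/12 + 1/462)] = 0.68. The 95% CI spans a factor of exp(1.96 × 0.68) ≈ 3.8 either way.

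**The case against.** Several stronger readings are tempting, and the article does not support them.

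- *Three mutually contradictory lists.* Two of the three are example lists, so the omission of child cleaning from the baseline text shows nothing about the baseline denominator. Nappy changing and child cleaning may be the same event. The full list may be in the survey tool or the outcome appendix, which are not shown. What stands is the closed list against feeding and animal contact; the article's own text still has to be reconciled.
- *A different list at end line.* Nothing suggests it.
- *Adjustment for household repeats only.* Incorrect: the models also carry a village random effect, village size and the a priori covariates. Only the missing type term is accurate.
- *Season, or the baseline share of households with a child under 5 (68/150, 53/100, 50/100), biases the estimate.* All arms were surveyed in the same months, so a common seasonal shift largely cancels. The under-5 difference is at baseline, largely differenced out if stable, and compatible with chance (chi-square 1.49, 2 df, p = 0.48). Bias needs a change in mix that differs by arm, and none is shown.
- *The illustrative ORs estimate the bias.* They do not; the rates and shifts are assumed.

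It is also fair to say that chance variation in mix is noise carried by the standard errors, and that a spurious OR of 1.25 is small beside a CI spanning a factor of about 3.8. The intervention may itself change how often latrine events occur, which would make type partly post-intervention. Reported latrine use is already 96%, which limits that route. The pooled proportion is a legitimate target. These points limit the importance of the issue and shape the fix. They do not remove the contradiction, nor do they protect the OR against a systematic TA-specific shift in mix.

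**Conclusion.** The event denominator of a stated secondary outcome is contradicted within the article and must be reconciled. Separately, the model as stated pools opportunity types with no type term, so a change in event mix that differs by arm between rounds would shift the interaction OR without any change in behavior.

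The size cannot be taken from the article. Over the assumed rates it is an OR of 1.06 to 1.22 for a 5-point shift in one arm, 1.13 to 1.45 for 10 points and 1.25 to 1.91 for 20 points, and nil if soap use does not vary by type. The article shows neither that such a shift occurred nor that it can be ruled out. With soap use at 3.3% of events, modest absolute shifts become visible relative effects. Only the handwashing behavior outcome is touched; the primary outcome, sanitation coverage, is not.

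**What to change.** 1. State one closed list of opportunities, say whether nappy changing and child cleaning are the same event, and use that list in Data Collection, the outcome definition and Table 3, for both rounds.
2. Tabulate events and soap use by opportunity type, arm and round, so that a reader can see whether the mix moved.
3. Report the interaction OR from the event-level model with a fixed effect for grouped opportunity type (for example fecal contact, food or feeding, animal contact) **beside** the pooled OR. State that the adjusted OR targets behavior per opportunity, while the pooled OR also reflects any change in the mix of events.

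Cost: no new data if type was recorded for each event, as the outcome definition implies, and a few extra parameters. With 36 soap events at baseline, 7 of them in the CLTS arm, types must be grouped to avoid sparse cells or separation. If the intervention itself alters the event mix, the adjusted OR answers a slightly different question, which is why it should accompany the pooled OR and not replace it.
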